### Measures

#### Primary outcome measure

Breast-Q (reconstruction or mastectomy versions, as appropriate) [31] is a widely used measure of quality of life specific to breast reconstruction.

#### Secondary outcome measures

EQ-5D-5 L (a measure of health-related quality of life) [32] and ICECAP-A [33] capabilities (what participants want to be able to do in various key aspects of life), shared decision making (Decisional Conflict scale [34], CollaboRATE [35] and visual analogue scales) and Decisional Regret (Decisional Regret Scale) [36].

Cost-utility analyses will be undertaken from a funder perspective over the timeframe of the study. Resources used at each stage of shared decision making will be recorded using a study-specific resource use checklist tool, which will be used with prices from published sources to estimate unit costs. Costs will be expressed in 2017 prices and uprated in line with inflation. Funder incremental costs (shared decision making with PEGASUS versus usual care) will be related to incremental change in EQ-5D-5 L scores to estimate (cost per Quality adjusted Life Year gained):

• Cost per Quality-adjusted Life Year gained based on the EQ5DL scores

• Average cost of implementing PEGASUS per site

• Average cost per patient

• Cost per hour of shared decision making

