Women dissatisfied with the outcome of BR may seek further, corrective surgery (with implications for healthcare resources and distress for patients), and may maintain avoidance behaviours (e.g. intimacy, clothing choices) that BR was intended to reduce [6]. We surmise that if women have realistic expectations, then patient dissatisfaction, well-being and requests for additional surgery would improve. Although HPs need to ask women about their priorities and concerns [8], promote realistic expectations [12, 13], and support them making high quality decisions by empowering them through SDM [14], there are no interventions to help them elicit patients’ values, expectations and preferences. Instead, support typically focuses on information provision (e.g. websites, leaflets). However, increasing the amount of information available does not address erroneous expectations since it reinforces patients as passive recipients rather than actively engaged in setting clear, patient-centred goals (an approach associated with positive experiences and outcomes [15]. SDM has been heralded as a means of improving patient reported outcomes and satisfaction with cancer care [16] (particularly concerning preference sensitive decisions [17]) but implementation is difficult and slow [18]. Some decision aids for mastectomy patients are available [19, 20] but these are not BR-specific or focused around a face-to-face discussion centred on patients’ individual needs and the practicalities and possibilities of surgery. Nor do they explicitly help HPs and patients with the challenge of implementing SDM in this difficult and emotive situation. Clinicians report concerns that online interventions such as BRESDEX.com cannot be tailored to patients’ individual needs, and could replace nurses’ roles and induce patient anxiety if not provided under clinical supervision [20]. Recently, attention has shifted to decision coaching to facilitate patients’ preparation for SDM about preference sensitive decisions [21].

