### Aims of the study

To assess the efficacy of an intervention designed to:◦ elicit patients’ expectations of what reconstructive breast surgery will achieve◦ facilitate setting of patient-centred goals◦ facilitate discussion of these expectations and goals with the patient’s surgical team.
To explore whether the PEGASUS intervention improves patient reported outcomes (Breast Q) and reduces decisional conflict amongst women offered the option of breast reconstruction.To explore the economic costs of delivering the PEGASUS intervention compared with the costs of treatment as usual.To explore patients’ and health professionals’ experiences of using the PEGASUS intervention and its implementation within breast reconstruction services.

The research will be overseen and informed by the expertise of an advisory group consisting of patient representatives, a surgeon, clinical psychologist, specialist nurse, breast cancer charity representative and members of the research team.

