### Data storage/confidentiality

A data protection document describes the study’s safeguards for the storage and protection of confidential information, both held manually and on computers. This document is guided by the Caldicott principles for handling patient-identifiable information, The UK Data Protection Act (1998) [38] and Good Clinical Practice guidance [39]. All data will be treated as confidential. Only members of the research team who are also members of the breast reconstruction service at the participating sites will examine clinic and medical records in order to identify potential participants. Once consented, the research team based at the university may require access to participants’ medical records in order to collect and check health economic data. Permission to do this will be included on the participant consent form. Audio files (interviews and consultation recordings) and data will be stored on a password protected computer accessible only by the research team. Completed questionnaires and consent forms will be stored separately, in a locked filing cabinet.

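### The cost-utility analysis names only decision-making resources as costs and describes its effect as an EQ-5D-5L score change, which falls short of its stated funder perspective and cost per QALY

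*Protocol article*

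**What the plan says.** The economic analysis is set out in the protocol article under Secondary outcome measures.

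- **Perspective and horizon:** "Cost-utility analyses will be undertaken from a funder perspective over the timeframe of the study".
- **Resource use recorded:** "Resources used at each stage of shared decision making will be recorded using a study-specific resource use checklist tool". These quantities are then priced from published sources.
- **Ratio:** "Funder incremental costs (shared decision making with PEGASUS versus usual care) will be related to incremental change in EQ-5D-5 L scores".
- **Outputs:** the first is "Cost per Quality-adjusted Life Year gained based on the EQ5DL scores". The others are an average cost per site, an average cost per patient and a cost per hour of shared decision making.

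Three other sections bear on the scope of costs.

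- The Background gives the resource argument: "Women dissatisfied with the outcome of BR may seek further, corrective surgery (with implications for healthcare resources". It goes on to surmise that realistic expectations would improve requests for additional surgery.
- Aims of the study states the economic aim as "To explore the economic costs of delivering the PEGASUS intervention compared with the costs of treatment as usual".
- Data storage/confidentiality says that the university team may need access to "medical records in order to collect and check health economic data", with permission on the consent form. It does not say which data.

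EQ-5D-5L is collected at decision making and at 3, 6 and 12 months after surgery (Abstract, Methods; Procedure).

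**The concern.** **Costs.** A funder pays for the reconstruction, the stay, complications, readmissions and any corrective operation. The plan names none of these, while its effects run to 12 months after surgery. PEGASUS adds a coaching appointment (Procedure) and staff training (Intervention training), so a count limited to decision making tends towards a positive increment and cannot show the saving that the Background anticipates.

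**Effect.** A QALY is utility accumulated over time. A change in score between two dates ignores when the difference arose and how long it lasted.

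The main research question asks about effectiveness in patient-reported outcomes and in costs. A ratio of delivery cost to score change, reported as a cost per QALY, could mislead a funder in either direction.

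**Working it through.** The plan states no cost, QALY or ratio, so there is no economic figure to reproduce. Its power calculation concerns the Breast-Q and plays no part here.

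**Step 1. Scope of costs, section by section.**

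| Section | What it says about cost scope | Surgical care named as a cost? |
|---|---|---|
| Secondary outcome measures | Decision-making resources; PEGASUS versus usual care | No |
| Aims of the study | Delivery of PEGASUS against the costs of usual treatment | Not specified |
| Data storage/confidentiality | Records may be used for health economic data | Not specified |
| Background | Corrective surgery has resource implications | Named as a consequence, not as a cost item |

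Two sections leave room for a wider costing, but none specifies it.

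**Step 2. Effect on incremental cost (all inputs assumed).** Let D be the delivery cost per woman, r the absolute reduction in the corrective-surgery rate and c the cost of one operation. Then

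incremental cost = D − r × c.

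With D = £100:

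| r | c = £1,000 | c = £3,000 | c = £5,000 |
|---|---|---|---|
| 0 | +100 | +100 | +100 |
| 0.02 | +80 | +40 | 0 |
| 0.05 | +50 | −50 | −150 |
| 0.10 | 0 | −200 | −400 |

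The decision-making-only figure is +100 in every cell. The sign changes once r × c exceeds D; at £3,000 per operation that needs r above 100/3,000 = 0.033. The index procedure is not included in this table and could move the result either way.

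**Step 3. Score change against QALYs (all inputs assumed).** Let d3, d6 and d12 be the between-group utility differences at 3, 6 and 12 months after surgery, with no difference at baseline, and let g be the months from baseline to surgery. By the trapezoid rule,

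QALY difference = [ (0 + d3)/2 × (3 + g) + (d3 + d6)/2 × 3 + (d6 + d12)/2 × 6 ] / 12.

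For a difference of 0.05 from 3 months onwards with g = 0: (0.075 + 0.15 + 0.30)/12 = 0.0438.

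| Time course (d3, d6, d12) | Difference at 12 months | QALY, g = 0 | QALY, g = 3 |
|---|---|---|---|
| Present from 3 months (0.05, 0.05, 0.05) | 0.05 | 0.0438 | 0.0500 |
| Growing (0.0125, 0.025, 0.05) | 0.05 | 0.0250 | 0.0266 |
| Only at 12 months (0, 0, 0.05) | 0.05 | 0.0125 | 0.0125 |
| Early, then faded (0.05, 0.05, 0) | 0 | 0.0313 | 0.0375 |

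In the first three rows the score change is 1.0 to 4.0 times the QALY difference. In the last row it is zero although QALYs were gained.

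**Step 4. The same check with utilities by group (assumed, g = 0).** Take 0.75, 0.70, 0.78, 0.80 with PEGASUS and 0.75, 0.68, 0.75, 0.80 with usual care, at 0, 3, 6 and 12 months.

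- PEGASUS: 0.18125 + 0.18500 + 0.39500 = 0.76125.
- Usual care: 0.17875 + 0.17875 + 0.38750 = 0.74500.
- QALY difference: 0.01625. The score rises by 0.05 in both groups, so the difference in score change is 0.

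Setting g = 0 treats baseline as the day of surgery. In the plan, baseline is at decision making, the interval to surgery is not given, and both immediate and delayed reconstruction are included, so g will vary between women.

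**The case against.** The strongest reply is that a condensed article does not list every cost item. The checklist is never said to be the only source, the wording in brackets after the incremental costs may simply label the two groups, and both the records clause and the stated aim allow a wider costing. That stands: a reader might infer that surgery is deliberately excluded, but the documents show only that it is not named.

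A reader might also infer that no cost per QALY can be produced. The documents do not support this either. Cost per QALY is a listed output, EQ-5D-5L is measured four times, and the area-under-the-curve method could sit in the full analysis plan. Nothing fixes the denominator as a simple baseline-to-12-month change.

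It is also fair to say that the stated aim is exploratory and centred on delivery cost, which the per-site, per-patient and per-hour outputs serve directly; that the link to corrective surgery is offered as a surmise; and that any effect of PEGASUS on the procedure chosen is a reviewer's inference.

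What these replies do not remove is that the article states a cost scope and an effect measure, and both fall short of the analysis it announces. Cost scope is also a data-collection decision: a later analysis plan cannot use surgical resource items that were never extracted.

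**Conclusion.** The point holds as a mismatch to be reconciled. The plan announces a funder-perspective cost-utility analysis over the study period, names only decision-making resources as costs, and describes the effect as a score change. Taken literally, the ratio would omit corrective surgery, a main route to savings on the protocol's own reasoning, and its denominator would not be time-weighted.

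The size cannot be measured from the documents. Under the assumptions shown, the incremental cost per woman runs from +£100 to −£400, and a score change of 0.05 at 12 months overstates the QALY difference by a factor of up to 4. These figures show that the sign and scale of the ratio can change, not that they will. The Breast-Q comparison is unaffected.

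**What to change.** 1. For the cost-utility ratio, name as cost items, to 12 months after surgery, the index procedure, stay, complications, readmissions and corrective surgery, taken from the medical records covered by the consent form. Add PEGASUS training and coaching.
2. Define QALYs as the area under the EQ-5D-5L utility curve, using each woman's actual interval from baseline at decision making to surgery, and adjust for baseline utility. The adjustment matters because the groups are not randomised.
3. Replace the score-change wording so that it agrees with the listed cost per QALY.
4. Report the decision-making-only cost separately, labelled as the cost of delivery. This keeps the stated economic aim and the per-site, per-patient and per-hour outputs.

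The QALY change uses data already collected, apart from the date of surgery. The cost change needs extra record extraction for 180 women at five sites, which is modest but real work, because the article says only that record access may be required.

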### Analysis

The analyses will be described in detail in a full Statistical Analysis Plan but, in brief, the design permits a robust statistical analysis using a linear mixed model with random intercepts for longitudinal data, a one-way ANCOVA with baseline pre-op measure as a covariate, and t-tests for prior reasoned group comparisons. An adjusted ANCOVA will be used to account for the between-subjects non-equivalent groups design and this will prevent an overestimation of treatment effect due to measurement error. Primary analyses will be performed under multiple imputation using Multiply Imputed Chained Equations (MICE) and repeated on a complete basis. Data validity checks and missing values analysis will be undertaken prior to descriptive and inferential analysis. PEGASUS is intended for use with any surgical group and we will compare delayed with immediate reconstruction patients for any systematic differences in outcome.

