### Power calculations

The primary outcome measure is the Breast-Q (breast reconstruction) [31] with psychosocial wellbeing, sexual well-being, physical well-being and 5 satisfaction subscales applicable pre- and post-op and an expectations subscale applicable pre-operatively only. Sample size has been determined to ensure the simple comparison between the two groups 3–month post-operatively has at least 90% power (beta <= .20) using contemporary levels of significance (alpha = .05) in a two-sided test as this will ensure similar power requirements will be met for within group comparisons and for the anticipated interaction effect in the two-way ANOVA. An a priori power analysis based on a two-sided application of the independent samples t-test with an assumed lower estimate of a medium effect size (Cohen’s d = 0.5) indicates that at least 90% power would be achieved with a sample size of *n* = 90 per group. This stated power equates to at least 75% of women doing better in PEGASUS than they would have done with treatment as usual.

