We will ask all participants to complete the following self-report measures in the questionnaire booklet at baseline (i.e. pre-intervention for those in the PEGASUS condition, equivalent timing for those in the control condition) and 3, 6 and 12 months after surgery, together with visual analogue scales (VAS) to assess the extent to which expectations/goals have been met, and satisfaction with decision making and care. Measures will be available for completion in paper format and online. Statistical analysis will examine changes in the self-report scores over time.

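### The named random-intercept model assumes equal correlation between all visits, so if baseline is a modelled response, its group-by-time contrasts against baseline can be miscalibrated

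*Protocol article*

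**What the plan says.** The Analysis section opens with "The analyses will be described in detail in a full Statistical Analysis Plan but, in brief" and then names three methods. The first is "a linear mixed model with random intercepts for longitudinal data". Listed separately from it are the other two: "a one-way ANCOVA with baseline pre-op measure as a covariate, and t-tests for prior reasoned group comparisons". It names no random slope and no residual covariance. It does not say whether the baseline score enters the mixed model as a response or as a covariate.

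The Procedure section has four measurement times: one before surgery, and 3, 6 and 12 months after it. It adds: "Statistical analysis will examine changes in the self-report scores over time". The Power calculations section sizes the trial so that "the simple comparison between the two groups 3–month post-operatively has at least 90% power", and expects similar power "for the anticipated interaction effect in the two-way ANOVA".

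**The concern.** A random intercept with independent residuals implies compound symmetry: equal variances, and one common correlation for all six pairs of visits. That is doubtful here. Surgery lies between baseline and every later visit, so a pre-operative score may well predict post-operative scores less closely than these predict each other.

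Where that is so, the model averages two different within-woman variances. The average is too small for a change from baseline and too large for a change between two post-operative visits. Tests of whether the groups change differently from baseline are then too liberal, and tests of whether an effect fades between follow-up visits are too conservative. Multiple imputation does not repair this, because the same model is fitted to each completed data set and its standard error is carried into the pooled result.

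The article makes baseline as a response the natural reading, though not a proven one. It speaks of change over time and of an interaction, and it lists the analysis with baseline as covariate separately from the mixed model.

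**Working it through.** **The plan's own figure.** Inputs from Power calculations: 90 per group, d = 0.5, two-sided alpha 0.05. The noncentrality is 0.5 × √(90/2) = 3.354, and Φ(3.354 − 1.960) = 91.8%. The noncentral t gives 91.6%. The stated power of at least 90% is reproduced. It concerns one visit only and involves no correlation between visits.

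**Inputs for the check.** From the article: 90 women per group, four visits, alpha 0.05. Assumed: equal variances σ², complete data and no group effect; correlation *rb* between baseline and each post-operative visit; correlation *rp* among post-operative visits.

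**Formulas.** Three of the six pairs have correlation *rb* and three have *rp*, so the random-intercept model uses a within-woman variance of σ²(1 − (rb + rp)/2). The ratio of true to model variance is:

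- one visit against baseline: (1 − rb) / (1 − (rb + rp)/2)
- mean of the three post-operative visits against baseline: (1 + (1 + 2rp)/3 − 2rb) / ((4/3)(1 − (rb + rp)/2))

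The actual size of a nominal 5% test is 2(1 − Φ(1.96/√ratio)).

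**Example, rb = 0.3 and rp = 0.7.**

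- One visit: 0.7/0.5 = 1.4, so the size is 2(1 − Φ(1.656)) = 9.8%.
- Mean post-operative: 1.2/0.667 = 1.8, so the size is 2(1 − Φ(1.461)) = 14.4%.

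**Simulation.** 20,000 null trials per row, using the exact balanced-data form of the random-intercept test:

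| rb / rp | Ratio, one visit | Ratio, mean post | 3 months vs baseline | Mean post vs baseline | 3-df interaction |
|---|---|---|---|---|---|
| 0.6 / 0.6 | 1.00 | 1.00 | 5.3% | 5.0% | 5.3% |
| 0.5 / 0.6 | 1.11 | 1.22 | 6.1% | 7.2% | 4.9% |
| 0.6 / 0.7 | 1.14 | 1.29 | 6.9% | 8.4% | 5.2% |
| 0.5 / 0.7 | 1.25 | 1.50 | 7.8% | 10.7% | 5.5% |
| 0.4 / 0.7 | 1.33 | 1.67 | 9.2% | 12.7% | 6.1% |
| 0.3 / 0.7 | 1.40 | 1.80 | 9.6% | 14.6% | 6.1% |
| 0.1 / 0.8 | 1.64 | 2.27 | 12.7% | 19.5% | 8.0% |
| 0.7 / 0.6 | 0.86 | 0.71 | 3.4% | 2.2% | 5.3% |

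**A different pattern.** Under AR(1) by visit with parameter 0.7, the mean of the six correlations is (3 × 0.7 + 2 × 0.49 + 0.343)/6 = 0.57.

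- 3 months vs baseline: ratio 0.30/0.43 = 0.70, size 1.9% (simulated 1.8%).
- 12 months vs baseline: ratio 0.657/0.43 = 1.53, size 11.3% (simulated 11.3%).

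For AR(1) parameters 0.5 to 0.8 the simulated ranges are 1.7 to 2.7% at 3 months, 9.4 to 12.4% at 12 months, and 5.9 to 6.5% for the 3-df test.

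**Between post-operative visits.** At 0.3/0.7 the ratio is (1 − 0.7)/(1 − 0.5) = 0.6, so the size is about 1.1% (simulated 1.2%).

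**Checks.**

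- A fitted mixed model at 0.3/0.7 with complete data rejected 7.3% for the 3-month contrast. With only 150 trials, the Monte Carlo error is about 2 points.
- A second run of 300 trials, with 15% missing at each post-operative visit, gave a mean model standard error of 0.160 against a true 0.182, and 8.3% rejection.
- The baseline-adjusted ANCOVA at 3 months held 4.8 to 5.2% in every scenario.

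**The case against.** The strongest reply is that the article gives a one-line summary and leaves detail to an SAP that was not available for this review. It does not say that the random intercept is the only covariance term, so a residual structure, robust standard errors or baseline as covariate all remain open. Covariance structure is ordinary SAP content. This stands in part. The article cannot be said to have excluded a richer structure, but it did not stay silent either: it named a random-effects structure, and the usual reading of that name is compound symmetry.

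A second reply is that the direction of the error depends on unseen data. This stands. Equal correlations give no inflation, the reverse ordering gives conservatism, and AR(1) makes the 3-month contrast conservative while inflating the 12-month one.

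A third reply is that the important comparisons are elsewhere. This also stands. The trial is sized on a single-visit comparison at 3 months, which uses only that visit's variance, and a baseline-adjusted ANCOVA is planned as well. The only interaction that the article mentions is the one in the two-way ANOVA, and its overall test is little affected.

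A reader might infer that the plan fixes a model that will declare a PEGASUS benefit two to three times too often. The documents do not support that. They give no correlations. A doubling for one visit against baseline needs a gap of about 0.4. The largest rates belong to the mean post-operative contrast, which the article never names. The 3-df test does not reach twice nominal in any scenario examined.

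**Conclusion.** The point holds in a conditional form. It needs two things that the article suggests but does not settle: baseline as a modelled response, and no residual structure beyond the random intercept.

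Given both, and post-operative visits correlated 0.7 with baseline 0.1 to 0.4 lower, nominal 5% tests run at about 7 to 10% for one visit against baseline and about 8 to 15% for the post-operative mean against baseline. At a lower post-operative correlation of 0.6 with a gap of 0.1, the rates are about 6% and 7%. The 3-df interaction test stays near 5 to 6%, and near 8% at the widest gap examined. Under AR(1) the 12-month contrast runs at about 9 to 12% while the 3-month contrast is conservative.

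The rates assume equal variances and, apart from one fitted-model check, complete data. They describe calibration only. Bias from the non-randomised design is a separate matter. The sizing comparison and the ANCOVA are sound on this point, so the change is worth making but is not critical to the trial's main comparison.

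**What to change.** In the Analysis section and the SAP, replace the random-intercept model by one of the following, and state which:

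- a mixed model for repeated measures over all four visits, with categorical visit, a group-by-visit term and unstructured within-woman covariance, fitted by REML with Kenward-Roger degrees of freedom; or
- the same model for the three post-operative visits, with the baseline score as covariate.

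Name robust (sandwich) standard errors as the fallback if the unstructured fit does not converge. If the SAP already specifies such a model, only the article's wording needs to be aligned.

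The cost is wording and a few lines of code, with no new data. The unstructured matrix has 4 × 5/2 = 10 parameters (3 × 4/2 = 6 for the second option) against 2 for the random-intercept model, which 180 women support easily. Intervals for some contrasts from baseline become wider, by the amount by which they were too narrow. For one visit this is √1.14 = 1.07 times at 0.6/0.7 and √1.4 = 1.18 times at 0.3/0.7. Intervals between post-operative visits become narrower in these cases.
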